## Abstract

**Background:**

Although the Internet is a promising medium to offer lifestyle interventions to large amounts of people at relatively low costs and effort, actual exposure rates of these interventions fail to meet the high expectations. Since public health impact of interventions is determined by intervention efficacy and level of exposure to the intervention, it is imperative to put effort in optimal dissemination. The present project attempts to optimize the dissemination process of a new online computer tailored generic lifestyle program by carefully studying the adoption process and developing a strategy to achieve sustained use of the program.

**Methods/Design:**

A prospective study will be conducted to yield relevant information concerning the adoption process by studying the level of adoption of the program, determinants involved in adoption and characteristics of adopters and non-adopters as well as satisfied and unsatisfied users. Furthermore, a randomized control trial will be conducted to the test the effectiveness of a proactive strategy using periodic e-mail prompts in optimizing sustained use of the new program.

**Discussion:**

Closely mapping the adoption process will gain insight in characteristics of adopters and non-adopters and satisfied and unsatisfied users. This insight can be used to further optimize the program by making it more suitable for a wider range of users, or to develop adjusted interventions to attract subgroups of users that are not reached or satisfied with the initial intervention. Furthermore, by studying the effect of a proactive strategy using period prompts compared to a reactive strategy to stimulate sustained use of the intervention and, possibly, behaviour change, specific recommendations on the use and the application of prompts in online lifestyle interventions can be developed.

**Trial registration:**

Dutch Trial Register NTR1786 and Medical Ethics Committee of Maastricht University and the University Hospital Maastricht (NL2723506809/MEC0903016).

## Background

Due to its high accessibility and its potential to reach large numbers of people, the Internet is considered to be a promising medium in the field of health promotion for offering tailored and targeted behaviour change programs to the general public [1-5]. Over the recent years, positive effects of online interventions applying computer tailored (CT) techniques have been reported [2,6,7], addressing physical activity [8,9], fruit and vegetable intake [10,11], smoking [12-15] and alcohol consumption [16,17]. However, in sharp contrast to these high promises, actual reach of these interventions is failing to live up to the high expectations [18-23].

Since public health impact of interventions is determined by their efficacy and exposure in the target group [24,25], it is important to optimize exposure to these interventions by conducting implementation studies and optimizing the methods by which they are disseminated to the general public. Earlier studies defined exposure as pertaining to three different aspects; accessing the intervention (first use), staying on the intervention for a substantial period of time (prolonged use) and revisiting the intervention (sustained use) [19]. Adoption, or first use, rates of online interventions are generally considered to be low [19,25,26], causing actual levels of engagement in the intervention as well as adherence to the intervention to be even lower. Since health behaviour change is a complex process, achieving sustained behaviour change is not only dependent on adoption of a behaviour change program. During a visit, intensive engagement in the program is essential to allow further notification of its content and involvement in its effective components [20,27]. Furthermore, the number of visits to an intervention is important. Due to a high dose-response relation [28,29], sustained use of the program is essential to further maximize its effect on subsequent health behaviour change [30,31].

The current project aims at optimizing exposure rates of a combination of several effective online CT programs, targeting physical activity, fruit and vegetable consumption, smoking and alcohol consumption, offered through the Internet. This combined CT program will be integrated in the Dutch Adult Health Monitor, a monitoring tool used by all Regional Public Health Service (RPHS) in the Netherlands in order to assess different aspects of general health and health related topics at fixed points in time. This integration will result in an online program that respondents of the Dutch Adult Health Monitor can turn to in order to obtain detailed and personalized information regarding their current health behaviour status, as well as personalized advice on how to improve their health by focusing on the key health behaviours.

Several theories underline the importance of different processes to foster effective diffusion of interventions [26,32]. These processes pertain to actual adoption (or first use) of the intervention by the target group and development of strategies to achieve sustained use of the intervention over time. In order to increase adoption rates of an intervention, it is imperative to obtain detailed profiles of those who successfully adopt a new intervention, i.e. so-called innovators or early adopters [25,26]. It is important to reach those people that benefit most from online lifestyle interventions, i.e. the people that engage in risk behaviours like smoking, excessive alcohol use, lack of physical activity or unhealthy eating patterns. By studying characteristics of first-time users and mapping the way the program is used and re-used, detailed knowledge on who adopts the intervention and on determinants of adoption can be obtained. Subsequently, this knowledge can be used to further optimize intervention content, as well as dissemination strategies in order to reach the target group. Furthermore, if first use is established, effective strategies need to be developed and tested in order to attain sustained use by first time users.

Currently computer tailored interventions are offered reactively to the public, implying a passive approach in which users themselves must undertake action in order to benefit from the intervention [33]. Prior research has, however, demonstrated that attaining visitors' loyalty to an intervention over an extended period of time is a very effortful process, entailing continuous endeavours to keep users satisfied and interested [20,22,29]. The suboptimal levels of exposure that are currently reached with the use of reactive strategies, combined with the high levels of attrition, indicate that the efforts put into ensuring visitor's loyalty are inadequate [27]. Therefore, focus should be directed towards developing and testing more proactive approaches in order to increase sustained use of effective behaviour change programs. Results from a recent review demonstrate the advantages of using periodic prompts as a relatively cost-effective method to encourage involvement in health promoting interventions [34]. However, since most studies included in this review refrained from using control groups and long-term data collection, to date, effectiveness of periodic prompting cannot be firmly established. Additional research to reliably assess the effectiveness of proactive strategies, such as prompting, is therefore needed.

In order to optimally disseminate the program, the present research project will thoroughly investigate adoption of an online CT lifestyle program and development of strategies to achieve sustained use. First, studying the adoption process will yield results on the level of adoption, determinants involved in adoption and characteristics of adopters and non-adopters as well as satisfied and unsatisfied users. A strategy aimed at increased and sustained level of use will be designed and tested. On that account the efficacy of a *pro-active approach *using periodic e-mail prompts in order to obtain sustained use of the intervention over time will be studied in a randomized control trial.

## Methods/design

The current project emphasizes the processes of first use (adoption) and re-use of a combined computer tailored online lifestyle program, by examining each process in a single study. First, a general description of the CT program will be provided, before proceeding to the detailed description of the separate studies.

The current project is approved by the Medical Ethics Committee of Maastricht University and the University Hospital Maastricht (NL27235.068.09/MEC 09-03-016), and is registered with the Dutch Trial Register (NTR1768).

### The CT program

The new CT program integrates established CT programs tested and proven to be effective in randomized control trials for increasing smoking cessation, promoting the intake of fruit and vegetables, increasing the level of physical activity and reducing the consumption of alcohol [16,35-38]. The multi-component CT program is embedded in an already existing channel; the Adult Health Monitor used by all Dutch RPHS's. This combination results in an online CT program that a substantial proportion of the Dutch population can use in order to obtain detailed and personalized information regarding the status of their current health behaviours, as well as personalized advice on how to positively change their health by focusing on key determinants of the five health behaviours.

#### The Adult Health Monitor

The Adult Health Monitor takes place with an interval of four years and serves as a monitoring tool used by the RPHS's to assess the overall level of health in the Dutch population by approaching a representative sample of the population to fill out a questionnaire assessing different aspects of general health (e.g. physical and mental health) and health related topics (e.g. social and physical environment) [39]. Physical health entails the five key behaviours targeted in this intervention; *physical activity*, measured by the Short QUestionnaire to ASsess Health enhancing physical activity (SQUASH) [40], *fruit and vegetable intake*, measured by the Short Questionnaire for Fruit and Vegetable Intake [41,42], *alcohol consumption*, measured by the Dutch Quantity-Frequency-Variability Questionnaire (QFV) [43] and *smoking*, measured by the abbreviated version of the Fagerström Test for Nicotine Dependence [44]. Results obtained through this Adult Health Monitor are communicated to the concerning municipalities, which subsequently use these as a basis for future health policies.

Integrating the new CT program into the Adult Health Monitor may have several benefits. Firstly, it can enable the RPHS's to optimize their public health education task; besides solely monitoring health behaviour, the RPHS's now have an opportunity to provide people with personalized advice on how to change their health behaviours. Furthermore, it may provide the random sample of adults included in the Adult Health Monitor an incentive for their participation and might serve as a cue to action for them to positively change their health behaviour. Since the current CT program is embedded in the Adult Health Monitor of the Provinces of Limburg, Brabant and Zeeland, with an approximate total reach of 100.000 inhabitants, this integration also provides an important access point for reaching a considerably large segment of the Dutch population with a lifestyle intervention.

#### Content of the CT program

The CT program uses a step-by-step approach to guide people towards behaviour change. After online completion of the Adult Health Monitor people are informed in detail on the embedded program and the accompanied studies. People that indicate to be interested in the program are subsequently linked to the program. During their first visit demographic data (age, gender, height, weight, religious background, ethnicity, educational level and income) and personal data concerning the target health behaviours, acquired through the Adult Health Monitor questionnaire, are transferred to the CT program and used to inform people on the current status of their health behaviours by comparing these to Dutch public health guidelines (i.e. being moderately physically active for 30 minutes at least 5 days a week, eating 2 pieces of fruit per day, eating 200 grams of vegetables per day, not drinking more than one (women) or two (men) glasses of alcohol a day and non-smoking). In case of discrepancies, people are alerted and provided assistance in changing their health behaviour(s) with help of CT advices available per behaviour.

Changing health behaviours with help of computer tailoring is the main component of the program. A CT module is available per health behaviour and within each module people have the opportunity to obtain personalized advices regarding the opted health behaviour. All health behavioural advices are adapted to individuals' characteristics by considering demographic, behavioural and social-cognitive variables [24,45,46]. Some variables, such as individuals' current health behaviours and characteristics of the respondent (gender), are directly obtained through the Adult Health Monitor. Other variables, such as cognitive variables with regard to the health behaviour (attitude, perceived social influence and self-efficacy), intention to change the health behaviour and planning strategies (action plans and coping plans) are assessed by using an additional tailoring questionnaire. All tailoring components are based on the Integrated Model for exploring motivational and behavioural Change (I-Change Model) [47].

### Intervention materials

Message content and algorithms of the CT advices are based on prior theory and evidence based CT interventions on physical activity, fruit and vegetable intake, alcohol consumption and smoking cessation [16,35,37,38,48]. Online questionnaires available for the health behaviours serve as basis for the CT advices. Attitude is measured by investigating respondent's level of agreement to a total of 6 statements regarding the pros (3 statements) and cons (3 statements) of the health behaviour under consideration (five-point scale; e.g. 'When I quit smoking, my health will improve', 'When I quit smoking, I will gain weight'). Social influence is measured by three different concepts; social norms, social modelling and social support. Social norms are assessed with one item, asking respondents to complete statements regarding perceived support from people in their environment (i.e., partner, family members, friends and colleagues) regarding the health behaviour (five-point scale; e.g. 'According to the people within my direct environment.... I certainly should not smoke'). Social modelling is assessed by one item asking participants how many people within their environment (i.e., partner, family members, friends and colleagues) engage in the health behaviour under consideration (five point scale; e.g. 'How many of your family members eat at least two pieces of fruit every day?'). Social support is measured with one item assessing the degree of support respondents receive from the people within their direct environment (i.e., partner, family members, friends and colleagues) to engage in the health behaviour (four-point scale; e.g. 'Do your friends stimulate you to be physically active?'). Self-efficacy is measured by means of 6 items asking participants to indicate whether they would be able to engage in (physical activity and nutrition) or refrain from (smoking and alcohol consumption) the key health behaviour when encountering difficult situations (seven-point scale; e.g. 'Will you be able to eat a sufficient daily amount of vegetables when other tempting alternatives are within reach?'). The intention to change behaviour is measured by means of two items. The first item is an extended version of the Stages of Change concept [49,50] using an algorithm consisting of ten stages varying from unaware to action, whereas the second item assesses the degree to which people are considering to engage in the key behaviour in the future; (seven-point scale; e.g. 'Do you intend to quit smoking in the future?'). Action planning is measured by three items asking respondents to indicate whether they plan to use a particular preparatory strategy when engaging in a certain behaviour (five-point scale; e.g. 'Are you planning to join a sports club?'). Coping planning is assessed by six questions asking participants to what degree they have made a specific plan regarding how to cope with difficult situations that might hinder execution of the health behaviour. These questions are based on the difficult situations used for the self-efficacy items (five-point scale; e.g. 'I have made a detailed plan to refrain from smoking when I just finished a meal.').

### Study 1: Assessing the adoption process of the CT program

The main goal of the first study is to assess the level of first time use of the new CT program, frequency of use, level of satisfaction with the new CT program by participants of the Adult Health Monitor 2009 and determinants of adoption and use. Furthermore, characteristics of users and non-users and satisfied and unsatisfied users will be investigated.

### Design

This is a prospective study, employing a longitudinal design. At baseline participants of the Adult Health Monitor interested in the new CT program receive feedback concerning their current health behaviour. In case of a negative discrepancy between the status of their current health behaviours and public health guidelines set for these behaviours participants are stimulated to change these behaviours with help of the CT program. During a period of three months, use of the CT program is monitored anonymously resulting in a detailed overview of number of first visits, revisits, and the specific health behaviours selected.

### Recruitment and procedure

The research sample consists of Dutch adults participating in the Adult Health Monitor 2009 of the Dutch Provinces of Limburg, Brabant and Zeeland. The RPHS's will invite a representative sample of inhabitants of the provinces North-Brabant, Zeeland and Limburg (+/- 100.000) by mail to participate in the Monitor. Participants will be offered the opportunity to fill out a written questionnaire, which is included, or to complete an online version of the Monitor questionnaire. Electronic completion will be highly encouraged since the new CT program is an online program only accessible for respondents participating via the Internet. Based on previous experiences with this Monitor it is expected that a response rate of approximately 33% will be reached, indicating that about 33.000 respondents will fill out the Adult Health Monitor.

After completing the Adult Health Monitor, all participants of the *online *version are introduced to the new embedded program, which is free of charge and consists of an opportunity to receive CT feedback about their health behaviour. Participants indicating to be interested in the new program will be asked to leave their e-mail address and receive an e-mail including an invitation to log in to the CT program with a personal login code and password approximately three weeks after completion of the Monitor. After logging on to the program participants receive detailed information on the goal and the content of both studies described in this protocol. After receiving this information, participants are asked to fill out an online informed consent form. Only those participants that consent to participation are directed to the new service. Subsequently, data on demographics and the five health behaviours obtained through the Monitor are transported to the new program, resulting in a personal overview in which an individual's current health behaviour status is compared to the guidelines set for these health behaviours. Within the program, five modules generating CT health advice are available to assist participants in changing their current health behaviour status when needed. Once respondents decide to leave the CT program after their first visit, they will be asked to fill out an additional questionnaire to assess their satisfaction with the program and their intention to revisit the program again in the near future (Figure 1).

**Figure 1 F1:**
[figure not shown]
**Flowchart study 1**.

### Inclusion and exclusion criteria for participants

Participants can be included in the current study when they are between 18 and 65 years and able to understand the Dutch language sufficiently. Moreover, they have to have access to the Internet. There are no explicit exclusion criteria stated for the current study.

### Measures

#### User characteristics

User characteristics are collected to produce a detailed user profile entailing information on personal characteristics, health behaviour status as well as socio-cognitive characteristics. Questions used in the Health Monitor pertaining to personal characteristics, included questions on gender, height, weight, marital status, religious background, ethnicity, educational level, current work status, and income. Furthermore, questions used in the Health Monitor pertaining to physical activity [40], fruit and vegetable intake [41], alcohol intake [43] and smoking behaviour [44] were used to assess health behaviour status. Finally, several determinants of health behaviour as mentioned in the I-Change model were used as socio-cognitive characteristics; intention, attitude, social influence, self-efficacy, action and coping planning.

#### Program evaluation

Satisfaction with the CT program will be assessed by using a total of five items; four items measuring the degree to which respondents regard the information provided within the program as new, personal, useful and encouraging (five-point scale; e.g. 'I think the information within the CT program is useful') and one item assessing overall satisfaction (ten-point scale; e.g. 'How satisfied are you with the current program?').

#### Intention to re-use the CT program

Intention to re-use the CT program is assessed by using a 10 point intention scale ('I intend to use this CT program again in the near future').

### Outcome measures

To measure the adoption level of the new CT program focus will be on level of first use, demographic and behavioural characteristics of users and non-users, satisfaction with the program, characteristics of satisfied and unsatisfied users, intention to re-visit the program and frequency of re-visits. In order to measure level of first use of the program, two dichotomous variables will be created; one indicating whether participants initiate a behaviour change module and one indicating whether participants finish the module. Initiating a module is labelled as "yes" when people fill out the first question of this module, which is the question concerning intention to change the specific health behaviour. Completion of a module is labelled as "yes" when people also fill out the final question of the module. Re-visiting of the program will be assessed monitoring whether participants log in to the program within a three month period after baseline (0 = yes/1 = no). Re-visits to the program will be measured by comparing the dates of log-in to the baseline date.

### Statistical analysis

First, general descriptive statistics will be used to describe personal characteristics of the participants, as well as main findings concerning current health behaviour status, adherence to the public health guidelines and socio-cognitive characteristics. Second, logistic regression analyses will be conducted with initiation of a module, completion of a module and revisiting of the program as dependent variables. Demographics, such as gender, height, weight, marital status, religious background, ethnicity, educational level, current work status, income, health behaviour status and cognitions (measured at baseline) are included in the model as predictors.

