#### Analyses

First, general descriptive statistics will be used to describe personal characteristics of the participants, as well as findings concerning current health behaviour status, adherence to the public health guidelines and socio-cognitive characteristics. Second, logistic regression analyses will be conducted with re-visits to the program and level of behaviour change as dependent variables. Furthermore, linear regression analyses will be conducted with number of re-visits, duration of re-visits and number of behaviours selected as dependent variables. Demographics, such as gender, height, weight, marital status, religious background, ethnicity, educational level, current work status, and income, health behaviour status and cognitions (measured at baseline) will be included in the model as predictors of the dependent variables.

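### Study 1's initiation model uses predictors that no non-initiator has, so it cannot be fitted as written; the completion model and the Study 2 models are weakened in related, conditional ways

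*Protocol article*

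**What the plan says.** **Study 1, Statistical analysis.** The plan states that "logistic regression analyses will be conducted with initiation of a module, completion of a module and revisiting of the program as dependent variables". After a list of demographics, it adds that "health behaviour status and cognitions (measured at baseline) are included in the model as predictors". One predictor list serves all three models. Study 1, User characteristics, names the socio-cognitive variables: intention, attitude, social influence, self-efficacy, and action and coping planning.

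**Study 1, Outcome measures.** Initiation is coded yes "when people fill out the first question of this module, which is the question concerning intention to change the specific health behaviour". Completion is coded yes "when people also fill out the final question of the module".

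**Where the predictors come from.** Study 1, Recruitment and procedure, says that after consent "data on demographics and the five health behaviours obtained through the Monitor are transported to the new program". Content of the CT program separates these Monitor variables from the rest: attitude, social influence, self-efficacy, intention and "planning strategies (action plans and coping plans) are assessed by using an additional tailoring questionnaire". Intervention materials describes these questionnaires as specific to each health behaviour and as the basis for the tailored advice.

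**Study 2.** Design announces a baseline measurement that covers intention, cognitive variables and planning. Randomization allocates people after they sign in, whether or not they open a module. Analyses repeats the predictor list: "health behaviour status and cognitions (measured at baseline) will be included in the model as predictors of the dependent variables".

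**The concern.** A predictor has to be observable whatever value the outcome takes. Here the intention item exists only for people whose initiation outcome is yes, because answering it is what makes the outcome yes. The other cognitions are described as coming from the same kind of questionnaire, and no other source is described for people who open no module.

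Determinants of adoption and use are among the stated goals of Study 1, and initiation is one of its two measures of first use. A model that cannot be fitted would probably be repaired after the data are seen, by dropping or imputing predictors in a way nobody has planned.

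The same predictor list raises two milder questions: whether the completion model loses its non-completers, and whether the Study 2 models lose randomised participants who never opened a module.

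**Working it through.** The plan gives no figure on this point to reproduce. The check traces where each predictor is collected relative to each outcome.

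**1. Initiation model**

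- Outcome Y = 1 if the module's intention item is answered, otherwise 0 (Study 1, Outcome measures).
- Predictor X includes intention (User characteristics; Statistical analysis).
- So X is observed only if Y = 1: P(X observed | Y = 0) = 0 and P(Y = 1 | X observed) = 1.

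Among usable records the log-likelihood is the sum of log p over people who all have Y = 1. It rises towards 0 as the intercept goes to infinity, so there is no finite maximum. Every 'no' outcome is lost, whatever the true initiation rate.

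Imputation does not help. No non-initiator contributes a cognition value, so imputed values would be borrowed from initiators, and the estimated association would reflect the imputation assumption rather than data.

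The result is the same if initiation is defined separately for each module. The questionnaires are behaviour-specific, so someone who skips the alcohol module has no alcohol cognitions even after opening the smoking module.

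**2. Completion model, among initiators**

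Every initiator has the opening intention item, and partial completers also have the items they reached. For illustration, assume 25 items in sequence, intention first, constant drop-out per item, and overall completion c among starters. None of these values is in the document. The share completing, among those who answered at least the first eight items, is c^((25−8)/24):

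| Assumed c | Completion, intention item known | Completion, first eight items known | Completion, all 25 items known |
|---|---|---|---|
| 0.50 | 0.50 | 0.50^(17/24) = 0.61 | 1 |
| 0.70 | 0.70 | 0.70^(17/24) = 0.78 | 1 |
| 0.90 | 0.90 | 0.90^(17/24) = 0.93 | 1 |

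With intention alone the outcome varies and the model can be fitted. Each further cognition required removes more non-completers. The outcome becomes constant only if all cognition items are required and the final question is one of them. The article does not say what the final question is.

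**3. Study 2 models**

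If cognitions exist only inside modules, and complete cases are used, the share of randomised people without a full set is 1 − (share starting) × (share of starters finishing). With assumed rates:

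- 70% start and 90% of these finish: 1 − 0.70 × 0.90 = 0.37.
- 30% start and 50% of these finish: 1 − 0.30 × 0.50 = 0.85.

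This range, 37% to 85%, reflects the chosen assumptions and does not estimate the loss. The document gives neither rate. Nor does it say that the Study 2 baseline measurement is the module questionnaire, or that complete cases will be used.

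**The case against.** The strongest counter-case has four parts.

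- **Completion.** A reader might infer that the completion model also fails outright. The documents do not support that: by the plan's own definition every initiator has answered the intention item, and the item order is not given. This part of the objection stands.
- **The trial.** A reader might infer that the randomised comparison excludes people who never open a module. Study 2, Design, states a baseline measurement of cognitions, and a condensed article need not describe every instrument. Missing-data handling is commonly left to an analysis plan that is not shown. This stands too, so the Study 2 point is conditional. On the other side, neither Recruitment and procedure section nor Randomization describes an instrument outside the modules that collects cognitions at baseline. Even if the loss occurred, it need not unbalance the arms, because the first prompt is sent three months after the first visit; it would narrow the analysed population and reduce power.
- **Source of cognitions.** Collection inside the module is explicit only for intention, and User characteristics names no source. That is correct, but intention alone is enough to make the initiation model circular.
- **Importance.** Initiation is one observational model among several aims. The planned comparison of users and non-users on demographics and behaviours can use Monitor data and is unaffected. This limits the damage but does not make the stated model estimable. The article fixes both the outcome definition and the predictor list, so the conflict is not a detail left to another document.

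**Conclusion.** The point holds for the initiation model. As written it is circular and cannot be estimated, because none of the 'no' outcomes has the listed predictors. For the intention item this follows from the definitions alone, with no assumed rates. For the other cognitions it rests on the article describing no source for non-starters other than the tailoring questionnaire.

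For completion the conclusion is narrower. Missing later cognitions are structurally tied to not completing, so a complete-case model with all cognitions drops non-completers selectively. It is not shown to be inestimable.

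For Study 2 the conclusion depends on two things the document does not settle: that the baseline cognitions are the module questionnaire, and that complete cases are analysed. If both hold, the models lose randomised participants who opened no module. The size of that loss cannot be derived from the document.

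**What to change.** - **Initiation:** fit the model on all consenting participants with Monitor-derived predictors only (demographics and behaviour status).
- **Completion:** fit it among initiators, with the same predictors plus the opening intention item.
- **Study 2:** state where the baseline cognitions are collected for participants who open no module. Unless they are collected from everyone, keep module-collected cognitions out of the primary randomised comparison so that all randomised participants are analysed.
- **Other cognition analyses:** report them as secondary and specific to each module.

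The change is to the model statements only; no new data are needed. The price is that associations with cognitions other than intention are estimated only among people who answered those items.
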